#### Statistical analysis population

The modified intention-to-treat (mITT) analysis set includes all participants who have been randomized and have completed outcome measures for the baseline (T0) and at least one post-intervention session (T1, either after high-intensity stimulation or after low-intensity stimulation) without major protocol violations. Since mixed-effects models allow missing data, we will conduct all analyses using mixed-effects models on the mITT analysis set. All participants who were randomized but not part of the mITT analysis set will be described. However, since the aim is to investigate the effects of high-intensity tVNS vs. low-intensity tVNS, it is crucial to have completed outcome measures for the baseline and at least one post-intervention session (high-intensity or low-intensity stimulation). We will impute missing values of covariate predictors to maximise the sample size for controlled analyses based on correlated covariates (e.g., body fat values based on BMI, sex, and age or single questionnaire scores).

Major protocol violations include:Changes in participant’s criteria that preclude safe use of tVNS.Insufficient (i.e., 0 minutes logged by the tVNS device) at-home stimulation during the intervention phases

Completion of the study is independent of interim analyses, and the study will continue until the planned sample size is reached. Interim analyses will use the mITT population but include only participants who have completed primary endpoint data at the time of the interim analysis. We record treatment expectations and blinding and will assess the extent to which the results depend on the treatment expectations.

#### Primary endpoints

The primary endpoints of this study are peripheral (circulating immune cells and cytokines) and central inflammation (DBSI), as well as motivation (effort invigoration and maintenance of the EAT and concurrent fMRI data). To evaluate stimulation-induced changes in high- vs. low-intensity tVNS, we will use linear mixed-effects models (LMEs) implemented in R using the ‘*lmerTest’* package [56], which are suitable for repeated measures. We will include covariates (all centered) such as BMI, age, sex, and stimulation order and perform model comparison (using anova(), *X*^2^ in R) to determine the final model structure. Primary outcomes are assessed at baseline and after each stimulation phase (high- and low-intensity; 14 d stimulation each). Stimulation-induced changes in primary outcomes will be compared between high- and low-intensity stimulation conditions.

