**Methods:**

To assess tVNS-induced effects on inflammation, motivation, and mood, we are conducting a single-blind, randomized crossover study in participants with an elevated BMI (target *N* = 60, 27–35 kg/m², 18–40 y). Participants will self-administer high- (active) and low-intensity (sham) stimulation daily (≥ 30 min) for ~ 14 days each (≥ 7 d washout). We will assess peripheral (cytokine levels, circulating immune cells) and central (diffusion weighted imaging) inflammation, motivation (using an effort allocation task during functional MRI), and mood at baseline and after each stimulation phase. During each stimulation phase, participants will complete daily ecological momentary assessments of mood and food choices. We will use mixed-effects models to evaluate differences in slopes of high- vs. low-intensity tVNS.

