## Methods

### Participants

We aim to include 60 participants aged 18 to 40 years with an elevated BMI (27–35 kg/m²), a range selected to reflect a population at increased risk for long-term consequences of obesity, including metaflammation. We will compensate for dropouts until the planned sample size is reached and 60 participants have completed all sessions. The sample size was determined to detect small-to-medium within-subjects effects (*d*_*z*_ ~0.40) with a statistical power of 1-*β* = 0.86, consistent with previous findings [69, 89]. Prior to participation, all individuals provide written informed consent after being given sufficient time for consideration and the opportunity to ask questions to the study team. Optionally, participants may consent to providing additional blood samples for the Mental Health Biobank Bonn using a separate consent form. Specific participant insurance is not provided; liability is only covered in cases of proven institutional negligence. The study has been preregistered at ClinicalTrials.gov (https://clinicaltrials.gov/study/NCT06954844) on March 21, 2025 and a statistical analysis plan has been uploaded to OSF. The first participant started on the 8th of April in 2025, and at the time of submission of this study protocol in July 2026, 27 participants had completed the study. Recruitment is expected to be completed in May 2027.

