After the washout period, an adapted session without neuroimaging takes place. First, we take a selection of the previously assessed anthropometric measures (BMI, waist-to-hip ratio, resting heart rate, and blood pressure) and fasting blood samples (glucose, insulin, triglycerides, high-density lipoprotein (HDL), low-density lipoprotein (LDL), HbA1c, and a standard differential blood count). In addition, participants complete two state VAS (at the beginning and end of the session). Participants receive the tVNS device configured for the second crossover condition and complete the intervention phase again for ~ 14 days. The study concludes with Session 4 analogous to Session 2. In addition to EAT earnings, participants receive either 80 € or partial course credit as compensation.

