#### Secondary and other prespecified endpoints

Secondary endpoints are tVNS-induced changes in mood (PANAS), the correlation of tVNS-induced changes in peripheral and central inflammation with tVNS-induced changes in motivation and mood, and whether inflammation is associated with motivational indices or mood indices (orthogonal to the effects of tVNS). Moreover, we will evaluate the broader impact of tVNS across behavioral and mood domains as secondary endpoints (wanting and exertion ratings, utility slopes, mood and motivation in daily life, anhedonia (SHAPS-D), depressive symptoms (BDI-II), and apathy (AMI)). Secondary endpoints will be analyzed using LMEs or robust regression models, as appropriate. For LMEs the same covariates and predictors as described in the section primary endpoints will be used. Secondary outcomes are assessed at baseline and after each stimulation phase. For some secondary outcomes, there is a second baseline measurement before the second stimulation phase. In these cases, we will adjust the model accordingly. Stimulation-induced changes in secondary outcomes will again be compared between high- and low-intensity stimulation.

Other prespecified endpoints are tVNS-induced changes in metabolic blood parameters (triglyceride-glucose-index, HOMA-Index, triglycerides, HDL, LDL, HbA1c, adiponectin, leptin, (acyl-)ghrelin, and GLP-1), body measures (BMI, waist-to-hip ratio, resting heart rate, blood pressure, and percentage of body fat), physical activity, and in eating behavior including decision weights in the food choice task. In addition, we investigate tVNS-induced changes in state ratings in daily life collected via EMA and tVNS-induced changes in self-reported interoception. Stimulation-induced changes in other prespecified outcomes will again be compared between high- and low-intensity stimulation. We systematically assess side effects and will investigate potential predictors of tVNS efficacy.

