#### Statistical threshold and software

All analyses and tabulations will be performed using MATLAB or R [73, 74]. Generally, we consider α < 0.05 as significant. For exploratory analyses as well as post hoc tests, we will account for multiple testing using the false discovery rate (FDR).

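### The primary outcomes have no second baseline, so the comparison is post-high versus post-low under no carryover, and a fixed period term should be in the model

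*Protocol article*

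**What the plan says.** The Abstract (Methods) announces the comparison as one of slopes: "We will use mixed-effects models to evaluate differences in slopes of high- vs. low-intensity tVNS". The section on primary endpoints compares stimulation-induced changes between the two conditions and fixes the timing: "Primary outcomes are assessed at baseline and after each stimulation phase (high- and low-intensity; 14 d stimulation each".

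The visit after washout does not supply a second baseline for these outcomes. On Session 3, Experimental procedure states: "After the washout period, an adapted session without neuroimaging takes place". The measures listed there are body measures, metabolic blood values, a standard differential blood count and state ratings. The legend of Fig. 2 places the inflammatory blood panel at Sessions 1, 2 and 4. The section on secondary endpoints confirms the pattern: "For some secondary outcomes, there is a second baseline measurement before the second stimulation phase".

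The primary model takes covariates such as BMI, age, sex and stimulation order, with the final structure chosen by model comparison. The stated protection against carryover is a washout of at least 7 days. The sample size section plans until "60 participants have completed all sessions", for "small-to-medium within-subjects effects (*d*_*z*_ ~0.40") "with a statistical power of 1-*β* = 0.86, consistent with previous findings".

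**The concern.** A slope for a stimulation phase needs a measurement at the start and the end of that phase. For the primary outcomes only the first phase has both. The change computed for the second condition also contains the first condition, the washout and whatever drifted meanwhile.

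Two things follow. First, a change labelled as due to the second stimulation would be mislabelled. Second, the comparison that remains depends on nothing of the first phase surviving into Session 4, and the primary model as described has no term that addresses either this or a period effect. If part of a real anti-inflammatory effect persisted, the low-intensity value in people who had high intensity first would be shifted towards the active value, and the trial would understate the effect.

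**Working it through.** **Inputs.** From the article: n = 60 completers, d_z = 0.40, power 0.86 (Participants); significance level 0.05 ("Generally, we consider α < 0.05 as significant"; sidedness not stated); phases of about 14 days and washout of at least 7 days (Experimental procedure). Assumed, because the documents give no figure: the share f of the high-intensity effect still present at Session 4, the size π of a period effect, the between-session correlation r, and an even 30:30 split of the two orders. Effects are in units of the SD of the within-person difference.

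**1. The plan's own figure.** Two-sided paired t-test, noncentrality 0.40 × √60 = 3.10, 59 degrees of freedom: power 0.862. The stated 0.86 reproduces. It assumes no carryover.

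**2. Time spanned.** First condition: about 14 days. Second condition: 14 + 7 + 14 = 35 days or more.

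**3. What the contrast is.** In completers, (post-high − Session 1) − (post-low − Session 1) = post-high − post-low. The baseline cancels, so the long interval does not itself bias the contrast.

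**4. Order and period.** Write τ for the effect and π for the shift from Session 2 to Session 4. The expected difference high minus low is τ − π with high first and τ + π with low first. With equal sequences the mean is τ. With unequal sequences a bias of π × (n_low-first − n_high-first)/60 remains. An order main effect is constant within a person, so it drops out of the difference and removes none of this. A period term does.

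Even with balanced sequences, an unmodelled π inflates the variance of the differences from 1 to 1 + π². At π = 0.5 the effective d_z is 0.40/√1.25 = 0.358 and power is 0.78, against 0.86 with period in the model.

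**5. Carryover.** If a share f persists from high intensity into Session 4 and none from low intensity, the high-first group contributes τ(1 − f) and the low-first group τ, so the mean is τ(1 − f/2) (period effect set aside). Power by noncentral t, 58 degrees of freedom:

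| f | Expected d_z | Shortfall | Power |
|---|---|---|---|
| 0 | 0.40 | 0% | 0.86 |
| 0.10 | 0.38 | 5% | 0.83 |
| 0.25 | 0.35 | 12.5% | 0.76 |
| 0.50 | 0.30 | 25% | 0.63 |

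In 150 simulated trials at f = 0.50, the mixed model gave a mean estimate of 0.31 (0.30 expected), identical with and without an order main effect. Read as a carryover test, the order effect has power of about 6% at f = 0.25 and 8–9% at f = 0.50 (r from 0.3 to 0.8).

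**6. First phase only.** ANCOVA of Session 2 on condition, adjusted for Session 1, 30 per group. With the within-person difference scaled to SD 1, the outcome SD is σ = 1/√(2(1 − r)) and SE = σ√(1 − r²) × √(4/60), on 57 degrees of freedom.

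| r | SE | Power at 0.40 | 95% CI half-width |
|---|---|---|---|
| 0.5 | 0.224 | 0.42 | 0.45 |
| 0.7 | 0.238 | 0.38 | 0.48 |
| 0.8 | 0.245 | 0.36 | 0.49 |

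This estimate is free of carryover, but its half-width exceeds the target effect of 0.40.

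**The case against.** The strongest reply has five parts.

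- **The long interval does no harm to the main comparison.** This stands. A reader might infer from the 35-day span that the high-versus-low estimate is biased; step 3 shows that it is not.
- **The statistical analysis plan is on OSF and is not shown.** This stands in part. It may hold a period term or a first-phase analysis, so one cannot say that the trial has no carryover-free analysis. It cannot create primary measurements at Session 3 or turn a Session 1 to Session 4 difference into a 14-day slope. Stimulation order might also be meant as position within the sequence. However, it is listed with BMI, age and sex and described at randomisation as which condition comes first, which reads as a property of the person.
- **Restating the estimand leaves the exposure to carryover unchanged.** True. The restatement describes correctly what is estimated; only the first-phase analysis avoids the assumption, and it is imprecise.
- **The carryover shares are hypothetical.** True. An effect would have to last at least about 21 days (7 of washout and 14 of second phase), and nothing in the article says that it does. In this scenario the bias is towards no effect.
- **No within-condition claim is planned.** True. Both endpoint sections compare high with low, so a reader who infers a planned claim about the second phase alone goes beyond the text.

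The common baseline is itself defensible. Simple change from each phase's own baseline would double the variance with equal session correlations, lowering d_z to 0.40/√2 = 0.28 and power to 0.58. Even with primary outcomes at Session 3, a between-sequence check there would have only about 7–16% power for 25–50% carryover.

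**Conclusion.** The slope wording does not fit the schedule for whichever condition comes second. The primary comparison is post-high versus post-low, unbiased by the long interval but valid only without carryover. The named order term neither removes a period effect from this comparison nor changes the estimate under carryover.

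The sizes are conditional. Omitting period costs power (0.78 against 0.86) if the period effect is half an SD of the within-person difference. Carryover of 10–50% would shrink the estimate by 5–25%. These rest on balanced sequences, carryover from high intensity only, and values that the documents do not supply. The documents do not support the stronger reading that carryover is present or that the trial's main estimate is invalid. The Session 3 differential count and state ratings are coarse and cannot rule out carryover in cytokines, cell panels, imaging or effort.

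**What to change.** 1. For the primary outcomes, replace slopes and stimulation-induced changes by an estimand of post-high versus post-low (Sessions 2 and 4), with Session 1 as baseline.
2. Keep period (first or second phase) as a fixed term in the primary model, exempt from model comparison.
3. Add a first-phase-only ANCOVA (Session 2 on condition, adjusted for Session 1) as a supportive sensitivity analysis, and label it imprecise: power about 0.36–0.42, half-width 0.45–0.49.
4. Add the missing second baseline and the no-carryover assumption to the limitations in the Discussion. The Session 3 differential count and state ratings may be reported descriptively by preceding condition, with no claim that they exclude carryover.

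If the OSF plan already contains items 2 or 3, align the article's wording with it. The cost is wording, one model term and one extra analysis of data already being collected, with no new visits or samples. With 27 of 60 participants reported as complete, this can still be fixed before the final analysis. The drawback is that the first-phase result will probably be inconclusive by itself.

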#### Secondary and other prespecified endpoints

Secondary endpoints are tVNS-induced changes in mood (PANAS), the correlation of tVNS-induced changes in peripheral and central inflammation with tVNS-induced changes in motivation and mood, and whether inflammation is associated with motivational indices or mood indices (orthogonal to the effects of tVNS). Moreover, we will evaluate the broader impact of tVNS across behavioral and mood domains as secondary endpoints (wanting and exertion ratings, utility slopes, mood and motivation in daily life, anhedonia (SHAPS-D), depressive symptoms (BDI-II), and apathy (AMI)). Secondary endpoints will be analyzed using LMEs or robust regression models, as appropriate. For LMEs the same covariates and predictors as described in the section primary endpoints will be used. Secondary outcomes are assessed at baseline and after each stimulation phase. For some secondary outcomes, there is a second baseline measurement before the second stimulation phase. In these cases, we will adjust the model accordingly. Stimulation-induced changes in secondary outcomes will again be compared between high- and low-intensity stimulation.

Other prespecified endpoints are tVNS-induced changes in metabolic blood parameters (triglyceride-glucose-index, HOMA-Index, triglycerides, HDL, LDL, HbA1c, adiponectin, leptin, (acyl-)ghrelin, and GLP-1), body measures (BMI, waist-to-hip ratio, resting heart rate, blood pressure, and percentage of body fat), physical activity, and in eating behavior including decision weights in the food choice task. In addition, we investigate tVNS-induced changes in state ratings in daily life collected via EMA and tVNS-induced changes in self-reported interoception. Stimulation-induced changes in other prespecified outcomes will again be compared between high- and low-intensity stimulation. We systematically assess side effects and will investigate potential predictors of tVNS efficacy.

#### Statistical threshold and software

All analyses and tabulations will be performed using MATLAB or R [73, 74]. Generally, we consider α < 0.05 as significant. For exploratory analyses as well as post hoc tests, we will account for multiple testing using the false discovery rate (FDR).

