**Discussion:**

This study uses a 14-day home-based tVNS protocol (≥ 30 min daily) accompanied by daily ecologocial momentary assessments to investigate mid-term effects on chronic low-grade inflammation, mood, and motivation. The multimodal study design including a comprehensive panel of peripheral and central inflammatory markers enables the integration of inflammatory and behavioral outcomes and will provide important evidence regarding the efficacy of tVNS in chronic inflammation, based on a study with sufficient statistical power. In addition, the study could provide pathophysiological insights into the link between obesity and symptoms of depression via inflammatory processes. Ultimately, the study will facilitate future research on vagus nerve stimulation to complement the current set of therapies in overweight and obesity.

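### Primary endpoints are multi-variable families held to the general 0.05 threshold, while the stated FDR rule names only exploratory and post hoc tests; the 0.86 power is a single-test figure

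*Protocol article*

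**What the plan says.** Under *Primary endpoints* the protocol article states: "The primary endpoints of this study are peripheral (circulating immune cells and cytokines) and central inflammation (DBSI), as well as motivation". Motivation is then spelled out as effort invigoration, effort maintenance and the fMRI data acquired during the task. This text names no lead variable, composite, order of testing or co-primary rule.

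Under *Statistical threshold and software* there are two relevant sentences. The first sets the default: "Generally, we consider α < 0.05 as significant". The second gives the only multiplicity provision: "For exploratory analyses as well as post hoc tests, we will account for multiple testing using the false discovery rate (FDR").

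Under *Participants* the sample size is justified by one calculation, for "small-to-medium within-subjects effects (*d*_*z*_ ~0.40") "with a statistical power of 1-*β* = 0.86". It is tied to no particular endpoint and mentions no adjustment. Dropouts are to be replaced: "We will compensate for dropouts until the planned sample size is reached and 60 participants have completed all sessions". The Discussion part of the abstract says the evidence will be "based on a study with sufficient statistical power".

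**The concern.** Read as written, the rule gives exploratory and post hoc tests more protection than the tests that carry the trial's main conclusion. Several variables sit in each primary domain, so one nominal p-value below 0.05 in any of them could be reported as a positive primary result for inflammation or motivation. The abstract speaks of evidence on efficacy, and the closing discussion raises a possible complementary therapeutic role, so a primary result would be put to confirmatory use.

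The power statement is affected too. A reader who meets 0.86 beside a list of primary families may take it as the power of the primary analysis. Once error is controlled over those families, power for the same effect is lower.

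**Working it through.** **Inputs from the protocol article.** Threshold 0.05 (*Statistical threshold and software*); 60 completers, dz about 0.40, power 0.86 (*Participants*); crossover, so a paired comparison (*Experimental procedure*). Sidedness is not stated; two-sided is assumed.

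**Step 1: reproduce the stated power.** For a paired t-test, df = 60 − 1 = 59 and the noncentrality is 0.40 × √60 = 3.098. The two-sided critical value at 0.05 is 2.001. The noncentral t distribution gives power 0.862, which matches the stated 0.86. A one-sided test would give 0.922, which does not match. The figure is therefore that of one unadjusted two-sided test.

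**Step 2: count the primary variables.** Two counts bracket the plan.

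- *One test per domain:* immune cells, cytokines, DBSI, effort task, fMRI = 5.
- *Each listed variable tested:*
  - Table 1 has 20 terminal cell subsets: 10 in T-cell panel 1, 4 in T-cell panel 2, and 6 among monocytes and dendritic cells.
  - There are 3 DBSI readouts (edema, cellularity, dendrite/axonal density).
  - There are 2 effort indices.
  - There are 2 main fMRI contrasts.
  - Total: 20 + 3 + 2 + 2 = 27.

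The count of 27 leaves out the cytokines, whose panel is chosen after data collection (Fig. 2 legend). It also leaves out parent cell populations, the second version of the effort task, and multiplication by brain region.

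**Step 3: chance of at least one false primary result when no effect exists.** With k independent tests at 0.05 it is 1 − 0.95^k. For k = 5: 1 − 0.95^5 = 0.226. For k = 27: 1 − 0.95^27 = 0.750, with 27 × 0.05 = 1.35 false positives expected. For correlated tests, k equicorrelated two-sided z statistics were used. The protocol gives no correlations, so r is an assumption.

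| k | r = 0 | 0.3 | 0.5 | 0.7 | 0.8 |
|---|---|---|---|---|---|
| 5 | 23% | 21% | 18% | 15% | 13% |
| 27 | 75% | 63% | 48% | 33% | 25% |

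**Step 4: power once error is controlled over five domains.** The first Holm step uses 0.05/5 = 0.01. With df = 59 the critical value becomes 2.662, and with noncentrality 3.098 the power is 0.668. Solving for the effect detectable with 86% power at that level gives dz = 0.486, against about 0.40 at 0.05. Keeping 0.86 at dz = 0.40 and level 0.01 would need 87 completers. The 0.668 is a floor for a given lead variable under Holm, because later steps use less strict levels.

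**The case against.** The best case for the plan has five parts.

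- **The count of 27 is not fixed by the protocol.** The primary endpoints are named as constructs, and Table 1 only lists which cells are measured. Subset-level follow-up could count as post hoc testing and so already fall under FDR. This stands, and it is why the size is given as a range starting at five tests. Even at that lower count the error is two and a half to four and a half times nominal (13% to 23% against 5%).
- **Immune markers are correlated.** This also stands. A reader might infer that a false primary finding is more likely than not, but the documents do not support that. It holds for 27 tests at low correlation, and fails for five tests or at correlations of about 0.5 and above.
- **The word *Generally* signals a default, and the statistical analysis plan on OSF, which is not shown, may add a rule.** It may, and nothing here claims that it has none. But the article states its own rule, and the only exceptions it names are exploratory and post hoc tests. If the OSF plan treats the primary family differently, the article's sentence needs aligning with it.
- **The power figure is not wrong.** Agreed. It is stated for an effect size and reproduces exactly. A reader might infer a miscalculation; there is none. What is missing is the label that it applies to a single test.
- **Secondary endpoints are also outside the FDR sentence.** A reader might count that as a second defect. Formal control over secondary endpoints is a matter of preference, and it is not part of this point.

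**Conclusion.** The point holds. As written, the multiplicity rule leaves the primary families at an unadjusted 0.05 while correcting less important analyses. The resulting chance of a false primary result is 13% to 23% with one test per domain and 25% to 75% with 27 tests. These ranges assume no true effect anywhere, equal pairwise correlations from 0.8 down to 0, and two-sided tests. Where the trial falls depends on correlations and on a number of tests that the article does not settle.

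The stated power is correct for one test and should not be read as the power of the primary analysis. With control over five domains, 60 completers give about 0.67 at dz = 0.40 for the first test, or 86% power at a dz of about 0.49.

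**What to change.** Amend *Statistical threshold and software* in one of two ways:

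1. State that the FDR rule also covers the variables within the primary family.
2. Name one lead variable or composite for each of the five primary domains (immune cells, cytokines, DBSI, effort task, fMRI). Test these five with Holm at a family-wise 0.05, and place the remaining variables under FDR. The fMRI domain must be kept in the set, since the protocol lists it as primary.

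The second option supports a firmer claim about a named endpoint. The first may cost less power, depending on how many effects are real.

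In *Participants*, add that 0.86 refers to a single two-sided test at 0.05. If Holm is chosen, also report about 0.67 for the first step at dz = 0.40, or a detectable dz of about 0.49. Qualify the abstract's power claim to match.

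Date the amendment and carry it into the OSF plan. It should disclose any interim analysis of primary endpoint data already done, because *Statistical analysis population* provides for such analyses and 27 participants had completed at submission. No new data are needed. The cost is a less favourable stated power.
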